#### Measures of therapeutic mechanisms

Therapeutic mechanisms include: *mindfulness skills*, measured by the Freiburg Mindfulness Inventory;^44^
*self-compassion,* measured by the Self-Compassion Scale Short Form;^45^
*rumination*, measured by the Ruminative Responses Scale-Short Form;^46^ and *social support,* measured using the Social Provisions Scale.^47^ Measures are administered at baseline, 6, 12 and 18 months.

#### Other measured outcomes

Additional exploratory outcomes, potential covariates and intervention-only outcomes are outlined in table 3.

### Data analysis and management

#### Sample size

Sample size was determined by power analysis using G*Power 3. The primary outcome is difference in accumulated relapse rate over 18 months. A previous relapse prevention study in youth MDD reported a relapse rate at an 18-month follow-up of 62% for TAU and 36% in the relapse prevention group (OR=2.9).^48^ Since *Rebound* will be compared against an enhanced TAU, we assume a smaller effect (OR=2.5), for which a total sample of 192 people is required to achieve 85% power (alpha=0.05). A total of 255 participants will be recruited, allowing for a 25% attrition rate. This compares favourably with the attrition rates in the *Rebound* pilot (7%) and is comparable at an 18-month follow-up to the Horyzons RCT (25%).^14 15^

#### Data management

The RPMS is used to manage all outcome data. The RPMS includes an electronic Case Report Form (eCRF). The RAs record participant-level data on an eCRF. These data are subsequently entered into the eCRF section of the RPMS. Self-report data are entered directly by the participant. The RPMS is accessed using a secure website and is stored on a secure server. It is designed to maintain the privacy and confidentiality of participant information and to ensure the integrity of the data. Access to RPMS is restricted to study personnel, and the level of access is dependent on the person’s role.

#### Analysis of outcomes

Primary analyses will be undertaken on an intention-to-treat basis. Group differences in accumulated relapse rate at 18 months (primary outcome) will be tested using Fisher’s exact test. The Cox proportional hazards regression model (survival analysis) will be used to model time to relapse and rate of remission in each group, which will also be used to derive the hazard function reflecting the instantaneous probability of relapse/remission at any time over the 18-month follow-up.^49^ Finally, group differences (*Rebound* plus TAU vs enhanced TAU) in change over time in the continuous secondary outcomes across the 18-month follow-up will be examined using random-effects models. Random-effects models allow for estimation of between-person differences (ie, group effects) in within-person slopes (ie, change trajectories in secondary outcomes) and are the preferred methods for analysing clinical trial data.^50^

Mechanism of action analyses will be conducted using a multilevel structural equation modelling framework to assess mediation.^51^ Specifically, person-specific slopes representing change over time in the proposed mechanism-of-action variables will be examined as mediators of the effect of treatment group (*Rebound* vs control) on risk of relapse.

Additional analyses will use multiple imputation to assess the robustness of the findings to the choice of method for handling missing data. Additional comparisons between treatment groups based on completers-only analyses will be conducted. Analyses will be undertaken in accordance with The International Council for Harmnonisation (ICH) 9 guidelines including a full analysis as well as per protocol set. The per protocol sample will be defined based on receiving a prespecified minimal exposure to the online intervention (ie, more than 16 logins over the 18-month intervention period).

The economic evaluation will comprise a cost-consequences analysis comparing the incremental costs of the *Rebound* platform (vs treatment as usual) to a wide range of incremental study outcomes (eg, QALYs, relapse rate). Inclusion of the AQoL-8D questionnaire facilitates the derivation of QALYs and enables a cost-utility analysis to be undertaken. A study-specific RUQ was adapted for this study from another RUQ frequently used in Australian mental health-related economic evaluations.^52^ The RUQ encompasses: community-based health service use; hospitalisations; accommodation services; medication and diagnostic tests; impacts on education and employment; and other relevant services. Best practice within-trial economic evaluation methods will be adopted^53^; and the comparative cost-effectiveness of the *Rebound* platform (vs treatment as usual) will be summarised using the incremental cost-effectiveness ratio metric (eg, cost per QALY). If the *Rebound* platform is found to be effective, then the lifetime and population cost-effectiveness of the intervention will be evaluated using modelling techniques.

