### Enrolment and randomisation

Participants are recruited from primary and specialist youth mental health services. In Victoria, study research assistants (RAs) attend weekly clinical review meetings at YMC and headspace services to identify eligible clients. In NSW, a study clinical liaison has been appointed at satellite sites to actively facilitate recruitment at the site. The study liaison attends clinical review meetings, engages with treating clinicians and screens clinical files to identify potentially eligible clients. The study liaison introduces the trial to the client and obtains consent to share contact details with Orygen. Young people can also self-refer via the study recruitment page on the Orygen website.

The RA contacts potential participants, provides a detailed explanation about the trial and offers to answer questions. All participants are required to provide informed, signed consent. Parental or legal guardian consent is required for participants under 18 years of age. Once consent is obtained, the participant is enrolled in the trial and a screening assessment to assess eligibility is conducted by the RA. Once eligibility is established, the baseline assessment is completed. After completing the baseline assessment, the participant is randomised by the RA via a secure online Research Project Management System (RPMS). The RPMS sends an automated email to the study coordinator and principal investigator, notifying them of the outcome of randomisation. The study coordinator informs the participant of the allocation. Participants are reimbursed for their time for each assessment completed.

The randomisation schedule is generated by a statistician independent of the study, programmed in the RPMS and not accessible by the study team. Participants are randomly assigned to the treatment condition via the RPMS using randomly permutated blocks with a 1:1 allocation ratio. Participants are stratified by current MDD status (current, partial or full remission), number of previous MDD episodes (≤ 2 or ≥ 3), age (<18 years and ≥18 years), sex at birth and by treatment centre.

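### The intention-to-treat label, the fixed Fisher's exact test and a sample size built on 192 completers do not describe the same primary analysis; an estimate that uses all quarterly follow-up should be primary.

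*Protocol article*

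**What the plan says.** Under Analysis of outcomes, the protocol article says "Primary analyses will be undertaken on an intention-to-treat basis". The next sentence fixes the test: "Group differences in accumulated relapse rate at 18 months (primary outcome) will be tested using Fisher’s exact test". Two other ways of handling incomplete follow-up appear later in that section, both outside the primary analysis: "Additional analyses will use multiple imputation to assess the robustness of the findings to the choice of method for handling missing data" and "Additional comparisons between treatment groups based on completers-only analyses will be conducted". A Cox model is planned for time to relapse, which is a secondary outcome.

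Under Sample size, the source rates are a "relapse rate at an 18-month follow-up of 62% for TAU and 36% in the relapse prevention group (OR=2.9"). The design assumption is "we assume a smaller effect (OR=2.5), for which a total sample of 192 people is required to achieve 85% power (alpha=0.05"). The inflation step follows: "A total of 255 participants will be recruited, allowing for a 25% attrition rate".

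Under Primary outcome and measure, relapse counts whenever it occurs in the 18 months after randomisation, and it is assessed every 3 months. Randomisation uses "randomly permutated blocks with a 1:1 allocation ratio".

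**The concern.** Cumulative relapse is unknown for anyone who leaves relapse-free before month 18, and Fisher's test has no place for censored follow-up. Three treatments of such people are available to a plain 2×2 table:

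- **A.** Drop every non-completer. This matches the sample size, but it is not intention-to-treat, and the article lists completers-only as an additional analysis.
- **B.** Keep relapses seen before dropout and drop relapse-free leavers. This pushes both relapse rates up.
- **C.** Count relapse-free leavers as not relapsed. This pushes both rates down.

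B and C distort the comparison in opposite directions when dropout differs between arms. That is plausible here: Rebound participants have weekly clinician contact for 12 months, while the control arm has a static website without clinician support. The single primary result could then depend on which treatment is used.

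**Working it through.** **1. Reproduce the plan's figures.** The inputs are control 62%, OR 2.5, 85% power, alpha 0.05 (taken as two-sided) and 1:1 allocation.

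- Control odds = 0.62/0.38 = 1.632. Rebound odds = 1.632/2.5 = 0.653, so the Rebound rate is 0.653/1.653 = 39.5%.
- The difference is 0.225 and the mean rate is 0.507. Uncorrected n per arm = [1.960·√(2·0.507·0.493) + 1.036·√(0.62·0.38 + 0.395·0.605)]² / 0.225² = 87.0.
- With continuity correction, n = (87.0/4)·[1 + √(1 + 4/(87.0·0.225))]² = 95.7, so 96 per arm and 192 in total, as stated. Exact Fisher power at 96/96 is 85.4%.
- 192/0.75 = 256, against the stated 255; 255 × 0.75 = 191.

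So the sizing is sound, and it counts on about 191 people with complete outcomes and nothing from the other quarter.

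**2. How many people have unknown status?** Assumptions, none of them in the documents: constant relapse hazard, dropout unrelated to relapse, and last attended visit spread evenly over months 0, 3, …, 15. With 18-month relapse risk p, the chance of being relapse-free after k visits is (1−p)^(k/6). Let g be its mean over k = 0 to 5. With dropout d:

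- unknown status = d·g
- rate under C = (1−d)·p + d·(1−g)
- rate under B = (rate under C) / (1 − d·g)

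| d = 25% in both arms | g | Unknown | B | C | True |
|---|---|---|---|---|---|
| Control | 0.694 | 17.3% | 65.5% | 54.2% | 62.0% |
| Rebound | 0.819 | 20.5% | 42.9% | 34.1% | 39.5% |

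For example, control under C is 0.75·0.62 + 0.25·0.306 = 0.542, and under B it is 0.542/0.827 = 0.655.

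**3. Power at the planned effect, 25% dropout in both arms** (simulation, 128/127, 6,000 runs): A about 86%, B about 90%, C about 89%, Kaplan-Meier 18-month risk difference about 91–92%. With all 255 outcomes known, Fisher would have about 95%.

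**4. No true effect (62% in both arms), dropout 35% control and 15% Rebound.** The imbalance is an assumption.

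- C: control 0.65·0.62 + 0.35·0.306 = 51.0%; Rebound 0.85·0.62 + 0.15·0.306 = 57.3%. Bias is 6.3 points against Rebound.
- B: control 0.510/(1 − 0.243) = 67.4%; Rebound 0.573/(1 − 0.104) = 63.9%. Bias is about 3.4 points in favour of Rebound.

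| Analysis | Bias (points) | Type I error |
|---|---|---|
| A, complete-case Fisher | 0 | about 4% |
| B, known relapses only | about 3.5, favours Rebound | about 7% |
| C, leavers counted as non-relapsed | about 6, against Rebound | about 16% (14–18% across runs and dropout patterns) |
| Kaplan-Meier difference | 0 | about 5% |

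At a milder 30% v 20%, C gives about 6–8% and B about 5%. With equal dropout and no effect, A, B and C all stay near 4%.

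**The case against.** The other side has real force on five points.

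- A reader might infer that the whole 25% is lost to Fisher's test. It is not. A relapse seen before dropout settles the outcome, so the unknown share is nearer 17–21%, and QIDS data may supplement the SCID.
- A reader might infer that the primary result will be biased or underpowered. With dropout independent of relapse, complete-case Fisher is unbiased even at 35% v 15%, and it gives the 85% power promised. The larger errors need both treatment B or C and an attrition gap that the documents do not give.
- A reader might infer that no rule for leavers exists. The article speaks of testing robustness to the choice of missing-data method, which presupposes one, and it refers to a statistical analysis plan that is not shown. The absence of the exact rule from an article is no finding.
- Kaplan-Meier is unbiased in these runs because dropout was simulated as independent of relapse. With an assumed shared frailty (SD 1) driving both, at 35% v 15%, it was biased by 2.5 points with 6.8% type I error. Complete-case Fisher did worse, at 5.7 points and 9.5%.
- It is tempting to add that multiple imputation cannot test the random-effects models because both assume missing at random. The article does not say which assumption its imputation makes, so that does not stand.

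What survives is what the article itself fixes. An analysis plan that keeps a plain Fisher table as primary and imputation as additional must still drop relapse-free leavers or assign them a status.

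**Conclusion.** The concern holds as a mismatch between three fixed elements: the intention-to-treat label, Fisher's exact test as primary with imputation only additional, and a sample size that counts on about 191 completers of 255.

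In the benign case the cost is efficiency: about 86% power where about 91% is available from data already scheduled. Under an assumed 20-point attrition gap, the treatments that keep partial data in a Fisher table give biases of about 6 and about 3.5 points in opposite directions, with type I error of 14–18% and about 7%. These sizes rest on constant hazards, evenly spread dropout and dropout independent of relapse.

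The stated N, power and alpha are right and need no change. This should be fixed; confidence is moderate, because the unseen analysis plan may already settle how leavers are handled.

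**What to change.** Keep the target, the 18-month cumulative relapse risk in all randomised participants, and make primary an estimate that uses every quarterly SCID. Either of these serves:

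- the multiple imputation already planned, with arm, the stratification factors, earlier SCID status and monthly QIDS in the imputation model; or
- an arm-wise Kaplan-Meier 18-month risk difference.

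Make complete-case Fisher supportive. Add a delta-adjusted sensitivity analysis that varies the leavers' relapse odds separately by arm, because both Kaplan-Meier and missing-at-random imputation are biased if dropout depends on unobserved relapse. If Fisher is kept as primary, the least that is needed is a stated rule for how relapse-free leavers enter the table, and a label that matches it.

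Make the change before outcomes are examined by arm. It costs wording and a little programming, with no new data and no change to the recruitment target.

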### Setting

Participant recruitment commenced in October 2019 at services in the North-Western Melbourne (Victoria, Australia) catchment, specifically the Youth Mood Clinic (YMC), a programme of Orygen Specialist Program (OSP) and headspace centres led by Orygen (in the Melbourne suburbs of Sunshine and Glenroy).^30 31^ Orygen is the world’s leading research and knowledge translation organisation focusing on mental ill-health in young people.

Orygen Digital, the digital mental health division of Orygen and Centre for Youth Mental Health at University of Melbourne, designs, delivers and evaluates evidenced-based digital services for youth mental health. In April 2020, Orygen Digital commenced implementation of the MOST platform across all Victorian youth mental health services as part of the Victorian State Government’s response to the COVID-19 pandemic and the recommendations of the Royal Commission into Victorian Mental Health system.^11^ Due to the overlap between study and implementation sites, participant recruitment from Victorian sites ceased in October 2020. Instead, satellite recruitment sites were established at headspace services in the Illawarra region, New South Wales (NSW), operated by Grand Pacific Health (Wollongong, Bega, Nowra, Goulburn) and two services within the South Eastern Sydney Local Health District (Bondi Junction Community Mental Health Centre and headspace Bondi Junction).

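### The primary test is an unadjusted Fisher's exact test although randomisation is stratified on five factors: valid and powered as planned, but less efficient than an analysis that follows the design

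*Protocol article*

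**What the plan says.** Under Enrolment and randomisation, allocation is made "using randomly permutated blocks with a 1:1 allocation ratio". The strata are given as: "Participants are stratified by current MDD status (current, partial or full remission), number of previous MDD episodes" (two classes), then "age (<18 years and ≥18 years), sex at birth and by treatment centre". The number of centre levels and the block size are not stated.

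Under Analysis of outcomes, the primary analysis is fixed: "Group differences in accumulated relapse rate at 18 months (primary outcome) will be tested using Fisher’s exact test". The additions to it are multiple imputation, a completers-only comparison and a per-protocol set. None of them is described as adjusting for, or stratifying by, the randomisation factors. Table 3 marks two measures as potential covariates, medication adherence and substance use; neither is a stratification factor.

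Under Sample size, 192 people give 85% power for an odds ratio of 2.5 at alpha 0.05, starting from a relapse rate of 62% under TAU. The target is raised to 255 for 25% attrition.

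**The concern.** Factors are put into a stratified randomisation because they are expected to predict outcome. An analysis that then ignores them tends to be conservative and leaves any remaining chance imbalance uncorrected.

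Two of the factors plausibly matter here. The Introduction describes a course that worsens with each episode. MDD status is tied to the endpoint itself: the trial enrols people who are currently depressed as well as people in partial or full remission, while relapse is defined as a return of full criteria. A person depressed at entry has to improve before a return can occur.

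Fisher's test is also conservative in its own right, because the table is discrete. At stake is precision in a trial whose recruitment closed in September 2023, where the choice of analysis is one of the few remaining ways to gain power.

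**Working it through.** **1. Reproduce the planned sample size.** Inputs from Sample size: control rate 0.62, OR 2.5, power 85%, alpha 0.05 (taken as two-sided, which reproduces the figure).

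- Control odds 0.62/0.38 = 1.632. Divided by 2.5 this is 0.653, so the intervention rate is 0.653/1.653 = 0.395.
- The usual two-proportion formula gives 87.0 per arm, rounded up to 88 (176 in total), without continuity correction. With the correction it gives 95.7, rounded up to 96 (192 in total).
- Exact enumeration of two-sided Fisher power gives 85.4% at 96 per arm, and 192 is the smallest total that reaches 85%.
- Attrition: 192/0.75 = 256, against the stated 255; 255 × 0.75 = 191.

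The plan's figure is therefore the Fisher sample size.

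**2. Cost of Fisher's conservatism alone** (exact enumeration over both binomials, 62% v 39.5%):

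| Arm sizes | Fisher power | Uncorrected chi-square power |
|---|---|---|
| 96 / 96 | 85.4% | 88.5% |
| 95 / 96 | 86.7% | 87.7% |

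At 96 per arm, Fisher's true two-sided type I error is 3.4% at a common rate of 0.4 or 0.6, and 3.6% at 0.5. The chi-square figures are 4.8% and 5.1%. The 3-point gap at exactly equal arms owes nothing to stratification, and one person's difference in arm size cuts it to 1 point.

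**3. Gain from adjustment.** The article gives no prognostic strength, so this part is assumed. Let b be the log odds ratio per step of MDD status and of episode class, with half of b for age and sex, and centre effects spread over ±0.5b. In the simulation, 255 people are randomised in stratified blocks of 4 (assumed) over nine centres, 25% are lost at random, and the marginal rates are held at 62% and 39.5%. There were 10,000 runs per scenario. The adjusted model is a main-effects logistic regression on all five factors.

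| b | Fisher | Adjusted, nominal Wald | Adjusted, calibrated to 5% | Calibrated gain over Fisher |
|---|---|---|---|---|
| 0 | 86.1% | 87.4% | 86.0% | about 0 |
| 0.35 | 86.3% | 88.9% | 87.3% | about 1 point |
| 0.7 | 86.3% | 90.4% | 89.0% | about 3 points |
| 1.0 | 87.2% | 93.1% | 92.0% | about 5 points |

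The nominal Wald test ran at about 6% type I error, so the calibrated column is the fair comparison. A chi-square test calibrated in the same way reached 87.6%, 88.1%, 88.9% and 89.5%. With nine centre terms in the model, adjustment therefore beats a calibrated unadjusted test only when the factors are fairly strong. That is a reason to pool centres.

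**4. How far stratification secures balance.** The four patient factors give 3 × 2 × 2 × 2 = 24 cells. Setting names nine services: three in Victoria ("specifically the Youth Mood Clinic (YMC), a programme of Orygen Specialist Program (OSP" and two "headspace centres led by Orygen (in the Melbourne suburbs of Sunshine and Glenroy") and six in New South Wales.

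- Two centre levels: 24 × 2 = 48 strata, 255/48 = 5.3 people each.
- Nine centre levels: 24 × 9 = 216 strata, 255/216 = 1.2 people each.

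In the nine-centre simulation, with assumed factor prevalences, about 134 strata are occupied. The 95th percentile of the arm-size difference is 23, against 31 under simple randomisation. For imbalance in a two-level factor it is 9 percentage points, against 12.

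**The case against.** The strongest reply is that nothing is broken. The sample size was set at the number Fisher's test needs, so its conservatism has already been paid for, and type I error is controlled. This stands. A reader might infer that the trial is underpowered or its primary result invalid; the article's own figures show neither.

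A second reply is that the power gain can be overstated by setting a nominal-level logistic model against Fisher. This also stands. Part of that gap is Fisher's discreteness and part is the Wald test running slightly above 5%. If the factors predict nothing, calibrated adjustment gains nothing.

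Third, 216 strata is an upper-end inference. The article does not say how treatment centre was coded, and the Victorian and New South Wales sites were not all recruiting together: "Due to the overlap between study and implementation sites, participant recruitment from Victorian sites ceased in October 2020". Nor has stratification failed, since it still reduces imbalance compared with simple randomisation.

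Fourth, a reader might infer that only a p-value will be reported. The article names a test and does not limit what is reported; estimates and intervals are commonly left to the SAP.

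What remains is that the article does not leave the primary test open. It fixes one that cannot take the stratification factors into account.

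**Conclusion.** The concern holds as a point about efficiency and consistency with the design. The stated primary analysis does not reflect the stratified randomisation, and a better one is available from data already needed to randomise.

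The size is modest. Power is 85.4% with Fisher at 96 per arm, which meets the plan. Calibrated adjustment adds about 0 to 5 points over Fisher. That range rests on assumed prognostic strength, factor prevalences, blocks of 4, nine centre levels and loss at random. The comparison with chi-square in step 2 is exact but sensitive to arm sizes. Some chance imbalance can remain, between the extremes of 48 and 216 strata, and an unadjusted test would not correct for it. This should be changed, but it does not threaten the validity of the trial.

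**What to change.** Before unmasking, by a dated amendment or in the SAP, make the primary analysis one adjusted for MDD status (three levels), previous episodes, age group, sex at birth and centre pooled to a few levels, for example state or service type. Two suitable forms are:

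- a logistic regression reporting a standardised risk difference and an odds ratio, each with a 95% confidence interval; or
- a Cochran-Mantel-Haenszel test on collapsed strata.

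Stratifying the test on every cell would be unworkable. Keep Fisher's exact test as a sensitivity analysis.

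No new data are needed and the randomisation is unaffected. There are two costs. A published primary test is changed late, since follow-up was due to end in March 2025, so the date of the change and the masking status must be documented. The all-factor Wald test may also run at about 6%, so use few centre levels and a likelihood-ratio, score or otherwise calibrated test.

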*Rebound* is a complex digital mental health intervention^23^ as it targets youth depression and prevents depressive relapse through the integration of several interacting components: (1) youth-friendly, evidence-based therapeutic content targeting mechanisms of mindfulness, self-compassion and rumination; (2) three types of human support (clinicians, peer workers and career consultants) applying evidence-based SDT-informed behaviour change techniques; and (3) a supportive online community of peers and peer workers sharing lived and living experience of mental ill-health, who aim to increase social support and decrease loneliness. *Rebound* has been iteratively developed with young people and a multidisciplinary team of clinicians, creative writers and developers over the past decade, using the Moderated Online Social Therapy (MOST) model.^24^,^26^ In a single-arm pilot trial (n=42), *Rebound* has been found to be safe, acceptable, and feasible and significantly improved depressive symptoms at a 12-week follow-up.^14^

The primary aims of the current study are:

To evaluate, via a randomised controlled trial (RCT), the effectiveness of the *Rebound* platform in preventing relapse of MDD in young people with MDD (aged 14–27 years).To evaluate the cost-effectiveness of the *Rebound* platform via a concurrent within-trial economic evaluation.To examine four therapeutic mechanisms (mindfulness skills, self-compassion, social support and reduced rumination).

The primary hypothesis is that relative to enhanced TAU, TAU plus *Rebound* will reduce the accumulated relapse rate over 18 months among young people with MDD. The secondary hypotheses are that relative to enhanced TAU, TAU plus *Rebound* will generate improvements in depressive symptoms, reduce time to relapse and time to remission, reduce remission rates, improve anxiety symptoms, and improve study and employment outcomes over 18 months; be more cost-effective; and help to prevent relapse in MDD by increasing mindfulness skills, self-compassion, social support and reducing rumination.

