#### Primary outcome and measure

The primary outcome is *relapse rate* (accumulated over 18 months) of MDD. Relapse will be defined as a return, for at least 2 weeks, of symptoms sufficient to meet DSM-5 criteria for MDD (as determined by the SCID-5-RV)^34^ at any time in the 18 months post randomisation. This definition of relapse is the one most commonly used in clinical studies.^39^ Measurement of relapse will be carried out every 3 months (ie, at 3, 6, 9, 12, 15 and 18 months). Telephone administration of the SCID is a valid method for measuring MDD.^40^ Data from the Quick Inventory of Depressive Symptomatology Self-Report^41^ may also be used to supplement the SCID assessment. A number of strategies will be embedded to promote participant retention, including a generous assessment window, flexible availability of RAs, minimal data collection at most timepoints and honing RA interview skills to minimise time commitment at larger assessment points.

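### The mediation model uses mechanism slopes with no lag and no cut at relapse, so it cannot tell a mechanism of relapse prevention from a consequence of relapse

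*Protocol article*

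**What the plan says.** The Protocol article (Analysis of outcomes) places the mechanism question in a multilevel structural equation model and names the mediator: "person-specific slopes representing change over time in the proposed mechanism-of-action variables will be examined as mediators of the effect of treatment group". The outcome in that model is the effect "on risk of relapse".

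Three other statements fix the timing:

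- Mechanism scales (Measures of therapeutic mechanisms): "Measures are administered at baseline, 6, 12 and 18 months".
- Relapse (Primary outcome and measure): an episode meeting criteria "at any time in the 18 months post randomisation", assessed every 3 months.
- Other repeated measures (Analysis of outcomes): "change over time in the continuous secondary outcomes across the 18-month follow-up will be examined using random-effects models".

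No sentence restricts the slope to scores obtained before relapse, lags the mediator, or limits the outcome to relapses after the mediator was measured. The Introduction lists examining the four mechanisms as the third of three primary aims, and places the matching hypothesis among the secondary ones.

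**The concern.** Mediation needs the mediator to change before the outcome. Here one slope per person is drawn from scores on both sides of the event. Rumination, mindfulness, self-compassion and perceived support are self-reports that a depressive episode can plausibly worsen. A person who relapses at month 4 then contributes three post-baseline scores, all taken after the relapse they are meant to explain.

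If relapse moves the scale, slope and relapse will be associated even where the scale has no influence on relapse. If *Rebound* also improves the scale directly, which the trial hypothesises, both legs of the mediation test can be satisfied without any mechanism. The multilevel framework does not by itself supply the missing time order. At stake is the interpretation of the mechanism aim, on which the Discussion relies when it expects the trial to advance models of relapse.

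**Working it through.** **1. Planning rates.** The Sample size section cites "a relapse rate at an 18-month follow-up of 62% for TAU and 36% in the relapse prevention group" and then assumes OR = 2.5. Control odds are 0.62/0.38 = 1.632; divided by 2.5 this is 0.653; 0.653/1.653 = 0.395. Rates of 62% and 39.5%, two-sided α = 0.05, 85% power and a continuity correction give 96 per arm, so the stated 192 is reproduced. The mediation analysis has no stated figure of its own.

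**2. Which scores follow relapse.** With visits at 6, 12 and 18 months, a relapse by month 6 precedes or coincides with all three post-baseline scores. A relapse by month 12 leaves at least two of the three after it. Any relapse before month 18 leaves at least the last one, if that visit is attended.

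**3. Share of relapses by month t.** The documents give no timing, so this is an assumption: a Weibull hazard with shape k, scaled to the 18-month rate p. Share = [1 − (1 − p)^((t/18)^k)] / p. Example: p = 0.62, k = 1, t = 6 gives (1 − 0.38^(1/3))/0.62 = 0.445.

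| k | by month 6, p = 62% / 39.5% | by month 12, p = 62% / 39.5% |
|---|---|---|
| 0.7 | 58.3% / 52.6% | 83.4% / 79.7% |
| 1.0 | 44.5% / 39.0% | 76.7% / 72.1% |
| 1.5 | 27.4% / 23.3% | 66.0% / 60.6% |

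**4. What reverse causation does to the planned model.** Simulation with N = 192, 1:1 allocation, constant hazards at the planning rates, a mediator at 0/6/12/18 months and 2,000 runs per row. The mediator has **no** effect on relapse; relapse lowers later scores by an assumed amount. Path a is the slope regressed on arm; path b is relapse regressed on arm and slope (logistic). False mediation means both paths are significant at 5%. In this table treatment has no direct effect on the mediator.

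| Shift after relapse | Duration | Path b falsely significant | False mediation |
|---|---|---|---|
| none | – | 4.6–5.5% | 0.4% |
| 0.3 SD | lasting | 58.6% | 4.6% |
| 0.5 SD | lasting | 95.1% | 13.0% |
| 0.8 SD | lasting | 99.9% | 24.0% |
| 0.3 SD | 6 months | 7.8% | 0.4% |
| 0.5 SD | 6 months | 11.8% | 0.4% |
| 0.8 SD | 6 months | 20.2% | 1.1% |

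Across further runs with N up to 255, false path b is about 55–100% for a lasting shift and 7–29% for a 6-month shift.

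**5. Adding a direct treatment effect on the mediator.** If *Rebound* raises the mediator by 0.4 SD over 18 months (N = 192 to 255), a lasting shift of 0.3, 0.5 or 0.8 SD gives false mediation in 48–65%, 87–97% and 96–100% of trials. A 6-month shift gives 5–27%. With no shift it is about 5%.

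**6. Time-ordered comparison.** Using mediator change over months 0–6 and relapse after month 6 in those relapse-free at month 6, false mediation was 2% or less in every scenario. Under a constant hazard, 96 × (0.38^(1/3) + 0.605^(1/3)) = 96 × (0.724 + 0.846) ≈ 151 of 192 remain.

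**The case against.** **The window is inferred.** The mediator sentence does not repeat the 18 months, and a statistical analysis plan not shown could add a lag or a cut at relapse. This is true. But the article goes beyond announcing a mediation analysis: it fixes the slope as mediator, on a schedule running to month 18, beside a parallel slope analysis across the whole follow-up, and adds no time restriction.

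**Relapse timing is not documented.** A reader might infer that the plan shows most relapses occurring early. It does not. People with current MDD are eligible and must improve before they can relapse. Letting half the sample become at risk only at months 2–8 (an assumption) lowers the share by month 6 from about 42% to about 27%. That lies within the range above, so only the range should be cited.

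**The bias may be small.** A reader might infer that any treatment that lowers relapse would show mediation through every mood-sensitive scale. The figures do not support that. Without a direct treatment effect on the mediator, most simulated trials show no false mediation on a given scale, and a shift lasting 6 months gives about 1% or less. A permanent shift is one end of the range, since episodes remit and the trial itself measures time in remission. This objection limits the size of the bias; it does not restore time order.

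**The low landmark rate proves little.** It shows that the method does not manufacture mediation, not that it can detect a true one; power for true mediation was not computed. This stands.

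**Conclusion.** The point holds for the mechanism aim. As stated, the model has no time order between mediator and relapse, and its result cannot separate mechanism from consequence. That conclusion rests on the documents, with the 18-month slope window read from the measurement schedule.

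The size rests on assumptions that the documents do not settle: when relapses occur, how far relapse moves each scale, for how long, and whether *Rebound* moves the scale directly. False mediation accordingly runs from about 1% or less (6-month shift, no direct effect) to about 90% or more (lasting shift of at least 0.5 SD with a 0.4 SD direct effect). No single figure in that range should be presented as the expected error.

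A reader might also infer that the trial's main result is compromised. It is not: the Fisher test of accumulated relapse and the sample size of 192 analysed and 255 recruited do not depend on this model.

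**What to change.** Specify as the main mechanism analysis a discrete-time or joint model in which the relapse hazard in each interval depends on the mediator value at the preceding assessment. Use only mediator values obtained before relapse. Adjust for the stratification factors and **baseline** QIDS; a later QIDS score could lie on the causal path.

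Add a month-6 landmark analysis (mediator change over months 0–6, relapse in months 6–18) as a sensitivity analysis. Describe any full-period slope model as association only.

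No new data are needed, since relapse is already assessed every 3 months and the mechanism scales every 6. The cost is analysis-plan wording, analysis time and the following:

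- **Precision.** Under a constant hazard with 192 analysed, expected relapses are 96 × (0.62 + 0.395) ≈ 97. About 192 − 151 = 41 fall by month 6, leaving about 56 that can inform mediation.
- **Early relapses.** There is little or no information on mediation in months 0–6, because the preceding mediator value is the baseline score.
- **Weaker early contrast.** If treatment raised the mediator steadily by 0.4 SD over 18 months, only 0.4 × 6/18 = 0.13 SD would be present at month 6, so the landmark analysis may have low power.
- **Selection.** The landmark version conditions on being relapse-free at month 6, a state reached after randomisation and open to treatment effects, so it is not a fully randomised comparison and should be reported as such.
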